### ***Data management and auditing***

Data will be collected both on paper and electronically. If participants return for follow-up, they will complete paper questionnaires; otherwise, they will use online forms. Paper surveys will be administered by an assessor who has received standardized training, and patients will also fill out their own paper questionnaires. Online surveys will be delivered through a designated app, and TUG testing will be conducted via video conferencing. Both groups may be provided with wearable devices for home use, which will be collected at the end of the intervention. A statistician not involved in the trial intervention will retrieve wearable device data, which two data administrators will then enter into anonymized databases equipped with logic checks (e.g., mandatory fields, response limits). These data will be organized into tables for statistical analysis. During recruitment, patients will receive comprehensive information about the trial's requirements and design, and they may withdraw at any time without giving a reason. Their progress will be tracked using a quality form, and those who drop out or discontinue the intervention will also have outcome data collected. Outcome assessors will document experimental procedures and data on a case report form, assigning each participant a unique code to protect privacy; only the assessors and the corresponding author will have access to these forms. All data entries will be verified twice by two independent assessors, after which the entries become non-editable. A Data & Safety Monitoring Committee is not required, given the low-risk interventions and the minimal likelihood of serious adverse events (incapacitating, life-threatening, hospitalization, or death). Auditing will involve on-site visits by independent supervisors twice a month to verify the presence and accuracy of investigation files, as well as checks on 20% of participants chosen at random to review source data, inclusion and exclusion criteria, missing scales, reporting, and informed consent.

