## **Setting & Recruitment**

Participants will be recruited from the Specialist Outpatient Clinic at West China Hospital, Sichuan University. Individuals who meet the eligibility criteria will be informed about the trial procedures and enrolled upon providing written informed consent; those who do not meet the criteria will receive standard treatment in accordance with the trial protocol. To ensure an

adequate sample size, standardized training and supervision will be provided to researchers, improving the success rate of informed consent acquisition. The trial aims to recruit 78 participants, and additional strategies (e.g., referrals from medical examination centers or relevant departments, poster campaigns) will be employed to facilitate timely enrollment. Recruitment will commence within one year of the scheduled enrollment date and will proceed based on site readiness. Details on data collection and intervention administration are available in Supplemental Material II. All eligible participants who agree to partake in the trial will be randomly assigned and briefed on the required procedures and written informed consent (accessible in Supplemental Material III) must be provided prior to enrollment. Baseline data for both groups will be gathered via a questionnaire administered before the intervention in Room 902 of the Special Needs Outpatient Department, collecting demographic information (e.g., gender, age, height, weight, occupation, education), potential causes of back pain, physical activity level, medical and exercise treatment history, duration of low back pain, severity of low back pain (current, worst, and least), level of functional impairment, and types of pain avoidance behaviors (see Supplemental Material II). Experienced physical therapists, who are independent of the trial design, intervention, and statistical analysis, will perform outcome measurements at baseline, after the 4-week intervention, and after the 8-week intervention, as illustrated in Figure 1.

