## ***Randomization and blinding***

Randomization will be conducted as participants are enrolled, using block randomization with a computer-generated random sequence (blocks of size four). A designated data manager, who is not involved in recruitment, intervention, or evaluation, will generate and securely store the random sequences in IBM SPSS, version 26.0.1. To conceal group allocation, an independent researcher not involved in the trial will place assignment codes into sequentially numbered, sealed, opaque envelopes according to the computer-generated random sequence. When each envelope is opened, participants will be assigned to either the control group or the trial group based on the corresponding “0” or “1” on the random number card. At enrollment, a physician not involved in randomization will assess potential participants, and the assignment group will be revealed onsite by opening the sealed envelopes, ensuring a 1:1 randomization ratio. Permuted blocks of size four will be used to maintain balanced allocation. Blinding physicians and volunteers to group assignments is not feasible, and participants are similarly unblinded due to self-reported outcomes. Assessors are also not blinded; however, to minimize bias, the trial hypothesis is not disclosed to either assessors or participants. The randomization list will remain secured (both physically and digitally), accessible only to the primary investigator and the designated data manager, thus maintaining its integrity throughout the study.

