## **CG Therapy**

The control group's interventions included paper-based exercise therapy and app-based patient education. At the initial diagnosis, physical therapists responsible solely for the intervention will provide patients with a printed exercise manual containing the same training exercises and frequency as the trial group, demonstrated once by the therapists. No further instruction will be offered during the subsequent eight weeks unless requested by the patient. The manual employs text and graphics to highlight essential elements, standards, and precautions for each movement. If patients encounter difficulties exercising at home, they may seek assistance at a designated partner community hospital or the main hospital, where physical therapists have received prior training. Over eight weeks, participants will complete 24 unsupervised self-training sessions (three times per week). In parallel, the control group will receive the same patient education content through an app that provides information once weekly for eight consecutive weeks. The app is configured only for patient education and does not grant access to the exercise training module.

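### Follow-up measurement mode (clinic paper form, or app form with video TUG) is set after randomisation by whether the patient returns; it may differ by arm and is not controlled

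*Protocol*

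**What the plan says.** The rule is in the protocol under Data management and auditing: "If participants return for follow-up, they will complete paper questionnaires; otherwise, they will use online forms". For the clinic route, "Paper surveys will be administered by an assessor who has received standardized training, and patients will also fill out their own paper questionnaires". For the remote route, "Online surveys will be delivered through a designated app, and TUG testing will be conducted via video conferencing". The TUG clause does not say whom it covers. In context it reads as the arrangement for people who do not come in.

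Baseline is on site. Setting & Recruitment states: "Baseline data for both groups will be gathered via a questionnaire administered before the intervention in Room 902 of the Special Needs Outpatient Department". The same section has physical therapists who "will perform outcome measurements at baseline, after the 4-week intervention, and after the 8-week intervention". Randomization and blinding says of them: "Assessors are also not blinded; however, to minimize bias, the trial hypothesis is not disclosed to either assessors or participants".

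TG Therapy gives the trial arm app-based exercise and a weekly video session. CG Therapy gives controls a printed manual and app-based education. If controls have difficulty exercising at home, "they may seek assistance at a designated partner community hospital or the main hospital".

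Statistical analysis names a group-by-time repeated-measures ANOVA, or a mixed model if assumptions fail, and puts the endpoint of interest at eight weeks. It names no term for mode. The protocol does not say that mode will be recorded as a variable or reported by arm.

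**The concern.** Anything decided after allocation that can change a measured score lies outside the protection of randomisation. Here that thing is the patient's choice to attend. It determines the form, whether an unblinded assessor is present, the setting, and for TUG the chair, floor, marked distance and timing.

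Two consequences are possible. If the share measured remotely differs between arms and mode shifts the score, part of the week-8 difference is a mode difference. Because baseline is on site for everyone, such an imbalance appears only at follow-up, so it falls on the group-by-time comparison. If the shares are similar and the shift is similar in both arms, the modes mainly add variability, including to within-patient change from a clinic baseline to a remote follow-up.

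TUG is the most exposed outcome: it is the only performance test, and a home video test differs physically from a clinic test. NRS and RMDQ are self-reported on either route, so a smaller shift is expected. What differs for them is the assessor, who is present only for the paper form, and for NRS the setting, since the scale asks about pain at that moment.

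**Working it through.** No figure in the protocol is at issue, so nothing is there to reproduce on this point itself. The group sizes used below come from Sample size: 58 completers, and 58 / (1 − 0.25) = 77.3, rounded up to 78 as stated. At 1:1 allocation that is 29 or 39 per arm.

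**What the text settles.**
- Mode at weeks 4 and 8 depends on attendance, so it is set after randomisation (Data management and auditing).
- Baseline is on site in both arms (Setting & Recruitment).
- Assessors are unblinded (Randomization and blinding).
- The scales are listed as self-reported (Table 3).

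**What it leaves open.**
- The return rate, overall or by arm.
- The size of any mode effect.

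**Size of a possible bias.** Let p_T and p_C be the shares measured remotely in the trial and control arms, and m the mode shift, taken as equal in both arms. Then

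bias = (p_T − p_C) × m.

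Both inputs are assumptions, since the protocol gives neither:
- Gap 0: bias = 0 whatever m is.
- Gap 10 points, m = 0.2 SD: 0.10 × 0.2 = 0.02 SD.
- Gap 20 points, m = 0.5 SD: 0.20 × 0.5 = 0.10 SD.
- Gap 50 points, m = 0.3 SD: 0.50 × 0.3 = 0.15 SD.
- Gap 50 points, m = 0.5 SD: 0.50 × 0.5 = 0.25 SD.

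**Effect on the two-sided 5% error** of a simple week-8 comparison with n per arm and no true difference (normal approximation): with d = bias / √(2/n), error = Φ(d − 1.96) + Φ(−d − 1.96). For example, at n = 29 and bias 0.25 SD, d = 0.25 / √(2/29) = 0.95, and the error is 15.9%.

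| Bias (SD) | 29 per arm | 39 per arm |
|---|---|---|
| 0 | 5.0% | 5.0% |
| 0.02 | 5.1% | 5.1% |
| 0.10 | 6.7% | 7.3% |
| 0.15 | 8.8% | 10.2% |
| 0.25 | 15.9% | 19.7% |

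**In natural units**, again with assumed shifts and gaps of 10 to 50 points:
- NRS, shift 0.5 point: 0.5 × 0.10 = 0.05 to 0.5 × 0.50 = 0.25 point. Against the protocol's 2-point MCID, used here only as a yardstick, that is 0.05/2 = 2.5% to 0.25/2 = 12.5%.
- TUG, shift 1 s: 1 × 0.10 = 0.1 s to 1 × 0.50 = 0.5 s.

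The upper ends need a large gap and a sizeable shift together. The sign is unknown, because neither the direction of the gap nor that of the shift is known.

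**The case against.** The strongest reply is that the harmful step is unproven. One rule is worded for both arms and no return rates are given. The direction is also uncertain:
- Controls have an app too, so both arms can complete an online form.
- The closer contact with therapists that the protocol expects in the trial arm could raise attendance there.
- Wearables, which both groups may receive, are collected at the end of the intervention, which could bring patients of either arm back at week 8.
- The in-person help named for controls concerns exercise difficulties rather than outcome visits, and may be at a community hospital. CG Therapy also allows further instruction on request without stating how it is given.

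All of this stands. A reader might infer that the comparison necessarily mixes treatment with mode and that both primary outcomes are confounded. The protocol does not support that; it supports only that mode may differ by arm and is not controlled.

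A second reply is that the remote option is useful. It limits missing data where 25% dropout is assumed, and it serves the commitment to collect outcomes from those who stop. This stands, and is why video TUG should stay available.

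Two further inferences should be resisted. One is that it is unclear whether the assessor's or the patient's paper score is analysed. Table 3 lists the scales as self-reported, which largely settles it. The other is that the main TUG comparison should use clinic values only. That would drop non-returners after randomisation and conflict with the intention-to-treat analysis the protocol makes primary.

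Finally, a sensitivity analysis by mode can reasonably sit in an SAP. But the rule that creates the mixture is a data-collection rule written in the protocol, and adjusting for mode afterwards would not fully repair it, because mode is chosen after randomisation and may depend on outcome.

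**Conclusion.** The point holds in limited form. Follow-up mode depends on attendance after randomisation, in an open-label trial with unblinded assessors and an on-site baseline, and the protocol neither fixes it nor states that it will be recorded or reported by arm.

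Bias in the week-8 difference requires that the remote share differ by arm and that mode shift scores, or that the shift itself differ by arm. The first is plausible from the way the two arms are managed but is not shown. Under the assumed ranges the bias runs from zero, with no gap, through 0.02 SD to 0.25 SD, where the 5% error would be about 16% to 20%. TUG, a secondary outcome, is the most exposed; NRS and RMDQ less so. The change is worth making because it is cheap, not because bias has been demonstrated.

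**What to change.** In Data management and auditing:

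- Collect every self-reported scale, in both arms, at each visit where Table 3 schedules it (baseline, week 4, week 8), by self-completion on the existing app form. Apply this also when the patient is in clinic, and drop the assessor-administered version. Table 1 already requires smartphone ability, and both arms use an app.
- Record mode and location at every visit and report them by arm.
- For TUG, make the clinic the default in both arms and keep video as a flagged fallback. Keep all TUG values in the main intention-to-treat analysis. Add a sensitivity analysis that sets video TUG values to missing and handles them with the planned multiple imputation.

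The cost is protocol wording, use of the app form in clinic, and one extra analysis. A single form does not remove the difference in setting for current pain, which some patients will rate after travelling and others at home. Recording location makes that visible but does not correct it.

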## Discussion

The primary objective of this study is to compare the efficacy of a telemedicine-supported structured exercise program with a paper-based exercise therapy program in improving pain among patients with CLBP in Chengdu, Sichuan Province, China. Current international guidelines strongly recommend exercise and behavioral therapy as first-line treatments for persistent chronic pain, emphasizing the importance of patient self-management. In line with these recommendations, the telemedicine-supported TG focuses on establishing a home-based self-management model.

Telemedicine replaces face-to-face physical therapist guidance with app-based monitoring, wearable devices, and the WeChat platform, thereby reducing time and geographic constraints while allowing patients to perform sustainable home-based exercises. This approach is reinforced by the pioneering use of wearable devices, which objectively document exercise duration (reflecting adherence) and capture patients' behavioral patterns. By drawing on diagnostic opinions from multiple pain experts, the wearable system can recommend personalized exercise regimens for CLBP patients. Changes in behavioral patterns before and after treatment serve as an objective indicator of therapeutic efficacy. The deep learning system can also track shifts in pain perception and fear of movement by monitoring protective behaviors, while weekly WeChat conferences bolster patients' trust in therapists and encourage adherence through group interactions. Patient education aims to alter pain-related beliefs, highlight the importance of healthy habits for pain relief, and promote an active lifestyle to manage ongoing CLBP progression. Beyond pain and physical function, this study also assesses pain cognition to capture a comprehensive view of outcomes.

In conclusion, this trial will investigate the impact of a telemedicine-supported structured exercise program on patients with CLBP in Chengdu, Sichuan Province, China. The results may offer a more effective home-based self-management model, ease the medical burden of CLBP, and inform public health and preventative strategies worldwide. The long-term sustainability and cost-effectiveness of telemedicine supported interventions will be the focus of future research.

## **Acknowledgments**

The authors are grateful to [name] and colleagues from Center of Biostatistics、 Design、 Measurement and Evaluation (CBDME) of West China Hospital for providing critical comments on the study design, sample size calculations, and for help in developing a statistical analysis plan. We would like to thank the technical support of the ShuKang company and [name] team of Tsinghua University.

## **Author contributions**

All authors made a significant contribution to the work reported, whether that is in the conception, study design, execution, acquisition of data, analysis and interpretation, or in all these areas; took part in drafting, revising or critically reviewing the article; gave final approval of the version to be published; have agreed on the journal to which the article has been submitted; and agree to be accountable for all aspects of the work.

## **Competing interests**

None declared.

## **Data sharing**

There are no plans for granting public access to the full protocol, participant-level dataset, and statistical code.

## **Funding statement**

This study was supported by the National Natural Science Foundation of China (82272599), Natural Science Foundation of Sichuan Province (2024NSFSC0533), Sichuan University “Research Special Project on the Comprehensive Reform of Innovative Educational Practices Enabled by Artificial Intelligence” (2024-44), 1.3.5 project for disciplines of excellence,

West China Hospital, Sichuan University (ZYGD23014), “Qimingxing” Research Fund for Young Talents of West China Hospital (HXQMX0113), Sichuan University West China School of Medicine Graduate Education Reform Project (HXYJS202415) and Science and Technology Bureau of Deyang City (Deyang Clinical Research Center for Rehabilitation Medicine, Mianzhu People's Hospital, 2023-64). The funders played no role in the design, conduct, or reporting of this study.

## **Patient and public involvement**

During the study design, patients were consulted to assess their confidence and expectations regarding telemedicine-based home rehabilitation. Feedback from a small group of patients informed the selection of primary outcomes and other study components. An advisory group was formed at the outset of the project, and investigators at each site are responsible for participant recruitment and trial execution.

## **Provisions for post-trial care**

If risks arise during treatment, the project team will address study-related adverse events at the participant’s expense. Should a serious adverse event be deemed related to the clinical research, the project team will cover the necessary treatment costs. Participants who can provide legally valid evidence of loss will receive appropriate financial compensation, including a 300-yuan subsidy for travel and housing expenses.

## **Confidentiality**

All research data will be labeled with a unique participant identification code. Only the study team will have access to the key linking these codes to individual identities. After the study concludes, the principal investigator will store and secure the code key in accordance with research guidelines. No patient-identifiable information will appear in any publications.

## Consent for publication

Written informed consent will be obtained from the patient for publication of this RCT and any accompanying images. A copy of the written consent is available for review by the Editor-in-Chief of this journal.

| Pain lasts 12 weeks or more.                                                                                                         | Cognitive impairment results in the inability to understand the physical therapist's instructions and the content of the app.                            |
| Pain intensity (when the worst pain) $\geq 3$ on the Numeric Rating Scale (NRS).                                                     | Pregnant or breastfeeding.                                                                                                                               |
| Ability to operate a smartphone.                                                                                                     | History of spine surgery.                                                                                                                                |
| Voluntarily participate in the trial and sign the informed consent.                                                                  | Patients who have received exercise therapy in the past three months for low back pain.                                                                  |
| Accepted randomization.                                                                                                              | Patients with severe cardiovascular and cerebrovascular diseases.                                                                                        |
| Candidates who meet all the above criteria will be included                                                                          | Candidates meeting any of the above criteria will be excluded                                                                                            |

616

617

618 **Table 2 Core stability training & Motor control training**

| Exercise (R=Repetition, S=Second)                                   | Sets and Repetitions per Week |     |           |     |
|---------------------------------------------------------------------|-------------------------------|-----|-----------|-----|
|                                                                     | 1-4 Weeks                     |     | 5-8 Weeks |     |
|                                                                     | Set                           | R/S | Set       | R/S |
| Core stability training                                      |                               |     |           |     |
| Abdominal breathing in the supine position (R)                      | 3                             | 5   | 3         | 10  |
| Dynamic hip bridge (R)                                              | 3                             | 10  | 3         | 15  |
| Side bridge (S)                                                     | 5                             | 10  | 5         | 20  |
| Plank support (S)                                                   | 5                             | 10  | 5         | 20  |
| Prone position contralateral extension (R)                          | 3                             | 10  | 3         | 15  |
| Four-point kneeling position alternate shoulder forward flexion (R) | 3                             | 10  | 3         | 15  |
| Four-point kneeling contralateral extension (R)                     | 3                             | 10  | 3         | 15  |
| Dead insect extension on the opposite side in a supine position (R) | 3                             | 5   | 3         | 10  |
| Motor control training                                       |                               |     |           |     |
| Pelvis forward and backward tilt in the supine position (S)         | 5                             | 10  | 5         | 20  |
| Stand on one leg with eyes closed (S)                               | 3                             | 5   | 3         | 10  |
| Side leg lifting with one leg (R)                                   | 3                             | 10  | 3         | 15  |
| Single leg micro squat (R)                                          | 3                             | 5   | 3         | 10  |
| Squat (R)                                                           | 3                             | 5   | 3         | 10  |

619

620 **Table 3 Overview of the measurements and timing of measurements**

| Domain      | Reporting     | Questionnaire | Baseline | 4 weeks | 8 weeks |
|-------------|---------------|---------------|----------|---------|---------|
|             | Method        |               |          |         |         |
| Demographic | Self-reported | Purpose built | √        | -       | -       |

|                                                |                 |                                   |   |   |   |
|------------------------------------------------|-----------------|-----------------------------------|---|---|---|
| characteristics                                |                 |                                   |   |   |   |
| Pain intensity                                 | Self-reported   | NRS                               | √ | √ | √ |
| Physical function                              | Self-reported   | RMDQ                              | √ | √ | √ |
|                                                | Walking ability | TUG                               | √ | √ | √ |
| Quality of life                                | Self-reported   | SF-12                             | √ | √ | √ |
| Psychopathological symptoms                    | Self-reported   | DASS21                            | √ | √ | √ |
|                                                | Self-reported   | EARS                              | - | √ | √ |
| Exercise compliance                            |                 | Movement completion rate          |   |   |   |
| Fear-avoidance in exercise & catastrophization | Events          | Frequency of protective behaviors | √ | √ | √ |
|                                                |                 |                                   |   |   |   |
| Adverse Events                                 | Self-reported   | -                                 | - | √ | √ |

621

622

623 **Notes:**

624 **Abbreviations:** LBP, Low Back Pain; CLBP, Chronic Low Back Pain; RCTs, Randomized  
625 Controlled Trials; TG, Trial Group; CG, Control Group; FITT-VP, Frequency, Intensity, Time, Type,  
626 Volume, Progression; IMUs, Inertial Measurement Units; RPE, Rating of perceived exertion; NRS,  
627 Numerical Rating Scale; RMDQ, Roland Morris Disability Questionnaire; TUG, Time up and go;  
628 SF-12, 12-item Short Form Health Survey; DASS21, Depression-Anxiety-Stress Scale; EARS,  
629 Exercise Adherence Rating Scale; SPIRIT, Standard Protocol Items: Recommendations for  
630 Interventional Trials; BMI, Body Mass Index; ITT, intention-to-treat; PP, Per-Protocol; SD,  
631 Standard Deviation; MCID, Minimum Clinically Important Difference

632

633

634 **Figure Legends**

635

636 Figure 1. Flow chart of the study

637 Figure 2. Intervention process at first visit.

638
